### Participants

#### Inclusion criteria

Inclusion criteria will include:-Registered births in the United States in 2023 at 24 to 42 weeks’ gestational age at birth

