### Primary study factors

-Change in maternal BMI from pre-pregnancy to birth-Maternal BMI (either pre-pregnancy BMI or BMI at birth as outlined below)

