### Variables

Mean and standard deviation (SD) will be used to describe continuous variables if they are normally distributed, otherwise median, and interquartile range (IQR) will be used. Categorical variables will be reported as numbers and percentages.

Gestational BMI gain in kgm^-2^ will be reported in the primary analysis. GWG in kg will be analysed for the sensitivity analysis.

Variables will be measured/described as follows:-Gestational BMI gain in kgm^-2^ (for the main analysis). Analysed as a linear spline with a knot at 5 kgm^-2^ based on preliminary analysis of 2022 data.-Self-reported pre-pregnancy BMI in kgm^-2^ (based on height and self-reported pre-pregnancy weight) classified according to the Institute of Medicine (IOM) groups [15]-Measured BMI at birth in kgm^-2^ classified into groups of the same size as pre-pregnancy BMI to account for expected weight gain during pregnancy-GWG in kg (for the sensitivity analysis)-Parity (categorized as nulliparous, or parous)-Maternal age in years (as a continuous variable, with linearity observed in the preliminary analysis of the 2022 data)-Gestational age at birth in weeks (categorized by gestational week)-Maternal height in cm (as a continuous variable, with linearity observed in the preliminary analysis of the 2022 data)-Maternal race (to be categorized as the dataset allows)-Maternal cigarette smoking during pregnancy (to be categorized as the dataset allows)-Payment type (public/private)-Trimester of onset of maternity care (first/second/third trimester/no antenatal care)-Maternal education (categorized as (i) 8th grade or less, (ii) 9th-12th grade, no diploma, (iii) completed high school or GED, some college credit or associate degree, (iv) bachelor’s degree, (v) masters degree, doctorate or professional degree)-Any fertility treatment used in conception (yes, no, unknown)-Diabetes in pregnancy (to be categorized as the dataset allows)-Hypertensive disorders in pregnancy (to be categorized as the dataset allows)-Previous preterm birth (yes, no)

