### Sample size

To estimate R^2^, pre-pregnancy BMI group and BMI gain were regressed on the other explanatory variables using equivalent US birth data for the preceding year (2022). As pre-pregnancy BMI was categorized according to IOM groups, dummy variables were created with normal BMI (18.5 to < 25) as the referent category, and each of these was regressed on the remaining dummy variables, the two BMI gain spline variables, and the other explanatory variables, resulting in five R^2^ estimations. As BMI gain was a linear spline with one knot, the two BMI gain spline terms were regressed on the five BMI group dummy variables, the remaining BMI gain spline variable, and the other explanatory variables, resulting in an additional two R^2^ estimations. These R^2^ estimations were repeated for nulliparous women only, resulting in 14 R^2^ estimations in total.

We specified an alpha value of 0.05 and beta value of 0.10, and a cesarean section rate of 18.17 % at the mean gestational BMI gain based on US birth data for 2022. This cesarean section rate was 27.40 % for nulliparous women only. We aimed to detect an increase in the cesarean section rate of one percentage point for each BMI category compared with the referent category (18.5 to < 25) (e.g., relative risk 19.17 %/18.17 %), and an increase in the cesarean section rate of one percentage point per kgm^-2^ of BMI gain. R^2^ values were used to calculate the variance inflation factor using the method described Signorini (1991) for calculating the sample size based on an exact Poisson Regression [19]. These calculations were performed using the pwrss package (Version 0.3.1) in R (Version 4.4.0).

The largest sample sizes required were:•For the full sample including nulliparous and parous women: required sample size = 570,014•For nulliparous women only: required sample size = 716,392

Based on the numbers of births in the 2022 data, we expect there will be enough births in the 2023 data to meet these required sample sizes

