As nulliparous women are an important group who contribute to the first/primary cesarean delivery rate, we will test for interaction (effect modification) between maternal BMI gain and parity, and maternal BMI and parity. If interaction is present (BMI or BMI gain have a different association with cesarean delivery depending on parity), then the primary analysis will be restricted to nulliparous women only and we will conduct secondary analyses for parous women.

For the primary outcome of cesarean delivery, backward stepwise Robust Poisson Regression will be used. The following variables will be included in the multivariable Poisson regression model as potential predictors of cesarean section:•Maternal BMI (not eligible for exclusion in the backwards stepwise regression).•Gestational BMI gain (not eligible for exclusion in the backwards stepwise regression)•Parity•Maternal age (continuous)•Gestational age•Maternal height•Maternal race•Cigarette smoking•Payment type•Trimester of onset of maternity care (4 categories: first, second or third trimester, or no•antenatal care)•Education (categorized)•Fertility treatment used•Diabetes (3 categories: pre-pregnancy, gestational, none)•Hypertension in pregnancy (dichotomous)•Interaction terms: BMI x parity and BMI gain x parity

Birthweight will not be included as an explanatory variable because it was considered that fetal weight may be on the causal pathway between BMI or BMI gain and cesarean delivery. Therefore, the relative risks for BMI or BMI gain for the primary outcome of cesarean delivery will include any indirect effect mediated through fetal weight.

If Robust Poisson Regression Models do not converge then alternative regression methods will be considered.

For secondary outcomes, all explanatory variables will be retained in the model. Stepwise backward regression will not be used. No interaction terms will be used.

For the secondary outcome of third or fourth degree perineal laceration, the data will be limited to vaginal births only and the following covariates will be used: BMI at delivery, BMI gain, parity, maternal age, gestational age, maternal height, maternal race, mode of delivery (unassisted/vacuum/forceps).

For the secondary outcome of trial of labour, the following covariates will be used: BMI at delivery, BMI gain, parity, maternal age, gestational age, maternal height, maternal race, payment type, education, trimester of onset of maternity care, use of ARTs, and gestational diabetes.

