For the secondary outcome of preterm birth, the same covariates will be used as for the primary outcome except gestational age will be removed and previous preterm birth will be added.

For the secondary outcome of NICU admission, the same covariates will be used as for the primary outcome of cesarean delivery.

For the uncommon or rare secondary outcomes of unplanned hysterectomy, maternal admission to the ICU, 5 min Apgar Score < 4, assisted ventilation immediately following delivery and for more than six hours, antibiotics for suspected neonatal sepsis, and neonatal seizure or serious neurological dysfunction, the same covariates will be used as for the primary outcome, if there are at least five events per variable. If there are fewer than five events per variable, then we will preselect a smaller group of the most relevant covariates or conduct a univariable analysis.

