#### Sensitivity analysis

(1)The primary analysis will be replicated using gestational weight gain instead of gestational BMI gain.(2)If multiple imputation is used, then the final multivariate fitted model from the imputed datasets will be replicated in the complete data for comparison.

We will report the results for the sensitivity analysis in pounds as well as kg.

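### The preterm birth model keeps total BMI gain to delivery as an explanatory variable, although early birth itself cuts that gain short, so gain will look protective even with no effect

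*Protocol article*

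**What the plan says.** All the relevant text is in the Protocol article.

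- **Exposure.** Primary study factors defines it as "Change in maternal BMI from pre-pregnancy to birth". This is a total accrued until delivery. Under Variables it is in kg/m²: "Analysed as a linear spline with a knot at 5 kgm^-2^ based on preliminary analysis of 2022 data".
- **Covariates reused.** The Analysis plan's list for cesarean delivery contains "Gestational BMI gain (not eligible for exclusion in the backwards stepwise regression", and gestational age.
- **No dropping.** "For secondary outcomes, all explanatory variables will be retained in the model".
- **Preterm model.** "the same covariates will be used as for the primary outcome except gestational age will be removed and previous preterm birth will be added".
- **Population.** "Registered births in the United States in 2023 at 24 to 42 weeks’ gestational age at birth".
- **Alternative exposure.** "The primary analysis will be replicated using gestational weight gain instead of gestational BMI gain". This is again a total, and it applies to the primary analysis only.

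Neither a weekly rate nor a gain standardised for length of gestation appears anywhere. Limitations does not mention the issue.

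**The concern.** Total gain to birth is fixed only when birth occurs, and the outcome here is that birth occurs early. Eligible pregnancies run from 24 to 42 weeks, so the time available to gain differs by up to 18 weeks. If women gain anything at all per week late in pregnancy, preterm births will on average show less total gain whether or not gain has any influence on when they deliver.

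The other covariate lists that the Analysis plan spells out (perineal laceration, trial of labour, NICU admission, the rare outcomes) contain gestational age, either directly or through the primary list. The preterm list cannot contain it, so nothing in that model absorbs the difference in duration.

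At stake is a precise inverse association between gain and preterm birth that could be reported as a finding. A larger sample makes the artefact more precise, not smaller. The section on uniqueness says that the results may bear on expectations about limiting gestational weight gain, so a spurious result of this kind would not be harmless.

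**Working it through.** **The plan's own figure.** The protocol states none for the preterm model. Its sample sizes (570,014 overall; 716,392 nulliparous) concern cesarean delivery. They cannot be reproduced, because the R² values and BMI-group prevalences are not reported. The point does not depend on them.

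**Step 1: is total gain really in the preterm model?** Yes. The model reuses the primary list with one stated removal (gestational age) and one addition (previous preterm birth). Gain is on the primary list, and secondary models retain every variable.

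**Step 2: inputs.**

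From the protocol: robust Poisson regression, six BMI groups, a gain spline with its knot at 5 kg/m², and gestational age omitted.

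Assumed, not in the documents:
- preterm means under 37 weeks, with a share of about 9%;
- mean gain of 4.5 kg/m² at 40 weeks, SD 2.2, falling by 0.08 per unit of pre-pregnancy BMI;
- pre-pregnancy BMI log-normal with median 26.5;
- late accrual r of 0.05 to 0.20 kg/m² per week. For orientation, 0.4 to 0.5 kg per week at a height of 1.63 m is 0.4/1.63² to 0.5/1.63², or 0.15 to 0.19 kg/m² per week.

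Length of gestation was generated independently of BMI and of each woman's gain trajectory, so the true relative risk (RR) is 1.

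**Step 3: hand approximation.** The simulated mean gestation was 33.9 weeks for preterm and 39.0 for term births, a gap of 5.1 weeks. The mean deficit in gain is then d = 5.1 × r. For a normal exposure with common variance, the log odds ratio per unit is −d/SD², with SD² = 2.2² = 4.84:
- r = 0.05: exp(−0.255/4.84) = 0.949
- r = 0.10: exp(−0.510/4.84) = 0.900
- r = 0.15: exp(−0.765/4.84) = 0.854
- r = 0.20: exp(−1.020/4.84) = 0.810

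With a 9% outcome the RR lies a little nearer 1 than these odds ratios.

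**Step 4: simulation in the protocol's form** (300,000 births per scenario, RR per kg/m² of total gain):

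| Late accrual, kg/m² per week | Mean gain, preterm / term | Pre-pregnancy BMI in model: below / above knot | Delivery BMI in model: below / above knot |
|---|---|---|---|
| 0.05 | 4.14 / 4.39 | 0.955 / 0.952 | 0.958 / 0.957 |
| 0.10 | 3.85 / 4.34 | 0.912 / 0.912 | 0.918 / 0.918 |
| 0.15 | 3.52 / 4.27 | 0.866 / 0.877 | 0.877 / 0.889 |
| 0.20 | 3.23 / 4.24 | 0.832 / 0.832 | 0.843 / 0.844 |
| Gain proportional to time | 3.52 / 4.30 | 0.929 / 0.640 | 0.939 / 0.647 |

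Every 95% confidence interval excludes 1. The closest to 1 is 0.945 to 0.969 (above the knot, delivery BMI, 0.05 per week). The simulation agrees with the hand calculation.

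**Step 5: is duration the cause?** With each woman's gain projected to 40 weeks in place of total gain, the RR returns to 0.993 to 1.008 below the knot and 0.995 to 1.007 above it, in all five scenarios.

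**Step 6: does weekly gain help?** In a separate null simulation (1,000,000 births), total gain gave an RR of 0.876. A weekly rate after week 13 gave 1.001 with a first-trimester allowance and 1.023 without one.

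**The case against.** The strongest reply concerns reach. Preterm birth is one of 21 listed secondary outcomes. The primary objective concerns cesarean delivery, and that model lists gestational age by week. The sample size, the AIC choice between the two BMI measures and the planned sensitivity analyses do not use the preterm model. The protocol speaks of describing and predicting, and makes no causal claim about preterm birth. All of this stands and limits the importance of the point. It does not rescue the gain coefficient: a predictor whose value is set by the timing of the outcome is no more usable for prediction than for explanation.

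A second reply is that the size is assumption-driven. That also stands. The accrual rate, preterm share and SD are not in the documents, and the proportional scenario gives a quite different pattern above the knot. Only the direction is robust.

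Three stronger readings are tempting and are not supported:
- **That removing gestational age is the error.** It defines the outcome, so it has to go and should not be put back.
- **That the cesarean result is compromised.** Gestational age is on that model's list and does not define its outcome.
- **That the artefact is several times the effect the study was sized to detect.** Any such multiple depends on the benchmark. Against the protocol's full-sample target (19.17/18.17 = 1.055, log 0.054), an RR of 0.955 (log −0.046) is about 0.9 times as large and 0.832 (log −0.184) about 3.4 times. That target also belongs to a different outcome.

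**Conclusion.** The concern holds for the preterm birth model and goes no further. Followed as written, the plan yields an inverse association between BMI gain and preterm birth when none exists. The direction requires only that women gain some weight per week late in pregnancy. For accrual of 0.05 to 0.20 kg/m² per week the spurious RR is about 0.96 to 0.83 per kg/m², conditional on the assumptions listed above. Whether pre-pregnancy or delivery BMI is chosen makes little difference to it. No planned sensitivity analysis would reveal it, because the only alternative exposure is another total, applied to the primary analysis alone. The gain coefficient in this one model is not interpretable; the primary analysis is unaffected.

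**What to change.** Before the 2023 data are analysed, amend the sentence on preterm birth, and make it an explicit exception to the rule that secondary models retain all variables. For this outcome, use pre-pregnancy BMI whichever BMI measure is selected for the cesarean model, omit BMI gain and delivery BMI, leave gestational age out, and keep previous preterm birth.

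If a gain measure is wanted, label it exploratory and adjust it for duration in one of two ways:
- weekly gain after a stated first-trimester allowance. The protocol lists only pre-pregnancy and birth measurements, so the allowance must be declared as an external assumption;
- a gestation-specific z-score from an external reference. It should not be standardised within week of birth in this file, because that equalises mean gain across weeks and forces the association to null.

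If total gain is kept in the model, say in the plan and in the report that its coefficient is not interpretable for preterm birth.

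The cost is one sentence, plus one derived variable if the exploratory measure is used. No new births are needed. The downside is that total gain is no longer reported as a predictor of preterm birth.

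### Week of birth is adjusted for in the newborn, hypertension and diabetes models, so their BMI relative risks omit the effect through early birth or condition on a consequence of the outcome

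*Protocol article*

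**What the plan says.** All of this is in the protocol article, mainly under Analysis plan.

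- The primary covariate list includes gestational age: "Maternal age (continuous)•Gestational age•Maternal height•Maternal race". Under Variables it is categorised by single week, so the adjustment is fine-grained.
- The general rule for the other outcomes is "For secondary outcomes, all explanatory variables will be retained in the model", without stepwise removal.
- For NICU admission: "For the secondary outcome of NICU admission, the same covariates will be used as for the primary outcome of cesarean delivery".
- For hysterectomy, maternal ICU admission, low Apgar score, both ventilation outcomes, neonatal antibiotics and seizure: "the same covariates will be used as for the primary outcome, if there are at least five events per variable". Below that threshold, "we will preselect a smaller group of the most relevant covariates or conduct a univariable analysis".
- The laceration and trial-of-labour models name gestational age directly: "BMI at delivery, BMI gain, parity, maternal age, gestational age, maternal height, maternal race".
- Only the preterm birth model is stated to leave it out: "the same covariates will be used as for the primary outcome except gestational age will be removed and previous preterm birth will be added".
- Hypertensive disorders and diabetes are listed under Secondary outcomes but have no covariate list of their own, so only the general rule governs them.
- For the primary outcome the plan reasons about mediators: "Birthweight will not be included as an explanatory variable because it was considered that fetal weight may be on the causal pathway". It adds that the relative risks are meant to include the indirect effect through fetal weight.

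The Sensitivity analysis section plans a weight-gain version and a complete-case version of the model. Neither omits gestational age.

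**The concern.** For newborn outcomes, early birth is a plausible main route from maternal BMI to harm, and the plan treats preterm birth as something BMI may cause. Holding week of birth fixed leaves only the part of the BMI association that does not pass through timing. A NICU relative risk near 1 from that model could be read as no excess newborn risk, when the adjustment itself removed the excess. The section on the study's uniqueness says it will examine how BMI influences outcomes, and such readers will expect the whole effect.

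For hypertensive disorders and diabetes the order is reversed. The condition arises first and helps to set when birth occurs. Week of birth is then a consequence of the outcome, and including it as a covariate moves the BMI relative risk toward 1.

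**Working it through.** The plan states no figure on this point, so there is none to reproduce. The numerical inputs below are assumptions, not document figures.

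**1. NICU effect that runs only through preterm birth.** Let p be the preterm risk in the reference BMI class, r the preterm relative risk for the higher class, a the NICU risk if preterm and b the NICU risk at term.

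Indirect RR = [p·r·a + (1 − p·r)·b] / [p·a + (1 − p)·b]

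Ranges: p 6% to 8%, r 1.2 to 1.6, a 40% to 50%, b 5% to 6%.

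- Lowest (p 0.06, r 1.2, a 0.40, b 0.06): (0.0288 + 0.0557) / (0.0240 + 0.0564) = 0.0845 / 0.0804 = 1.05.
- Highest (p 0.08, r 1.6, a 0.50, b 0.05): (0.0640 + 0.0436) / (0.0400 + 0.0460) = 0.1076 / 0.0860 = 1.25.

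A model that conditions on week of birth does not show this 5% to 25% excess.

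**2. NICU with a direct effect as well.** Assume 30% with high BMI, a direct BMI-to-NICU RR of 1.2, baseline preterm risk 7%, baseline NICU risk 5% at term, and a preterm-to-NICU RR of 8. The total RR is 1.2 × (1 + 7 × 0.07 × r) / (1 + 7 × 0.07).

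- r = 1.2: 1.2 × 1.588 / 1.49 = 1.28
- r = 1.4: 1.2 × 1.686 / 1.49 = 1.36
- r = 1.6: 1.2 × 1.784 / 1.49 = 1.44

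Simulated Poisson models (500,000 births each), with and without an unmeasured common cause of preterm birth and NICU admission, gave about 1.28 to 1.50 without gestational age and about 1.19 to 1.22 with it. The adjusted model returns the direct part only.

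**3. Hypertension as outcome.** Assume 8% baseline risk, preterm risk 7% × 1.2 for high BMI × 2.5 if hypertensive. Adding preterm status to the model moved the BMI RR from 2.03 to 1.96 and from 2.98 to 2.87. In the second case (2.98 − 2.87) / (2.98 − 1) = 6% of the excess is lost. With a true class 3 RR of 3.0 and a mild, moderate or strong shift to earlier birth, models with gestational week gave 2.97, 2.79 and 2.62. The losses are 0.03/2.0 = 2%, 0.21/2.0 = 11% and 0.38/2.0 = 19% of the excess. A separate run across weak to strong shifts gave 2.99 to 2.65, or 1% to 18%. The standard error of the log RR was about 0.012 with 716,392 births. The moderate case, ln(3.0/2.79) = 0.073, is about six standard errors; the mild case, ln(3.0/2.97) = 0.010, is less than one.

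**4. How far the rare-outcome exception reaches.** With about 47 parameters (a count that assumes the race and smoking categories), five events per variable needs 5 × 47 = 235 events. In 716,392 births that is 235 / 716,392 = 0.03%. Only very rare outcomes would escape the full covariate list.

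**5. What happens if gestational age is simply deleted.**

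- With delivery-BMI classes cut as planned and BMI given no effect on anything, simulated class 3 NICU RRs were about 0.82 to 0.83 without gestational age, and 1.01 with it.
- With BMI gain kept in a NICU model and its true RR set to 1.00, dropping gestational age gave a gain RR of about 0.91 to 0.93.
- For hypertension, dropping gestational age but keeping gain left the class 3 RR at about 2.72 against an assumed 3.0, with a spurious gain RR of about 0.93 (0.96 in another run).
- With pre-pregnancy BMI and neither gestational age nor gain, the NICU class 3 RR was about 1.15, against 1.01 as planned. The hypertension RR was about 3.1.

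**The case against.** The strongest objection is that gestational age is there for a reason. Primary study factors defines BMI gain from pre-pregnancy to birth, so gain grows with each week. The Analysis plan lets AIC choose delivery BMI for all later analyses, and the abstract hypothesises that BMI at birth may be the more relevant predictor. For either exposure, week of birth confounds the association, and deleting it can create the false protective result shown in step 5. This stands in full and shapes the fix.

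Second, the newborn models also keep diabetes and hypertension, two further routes from BMI to early birth. When BMI was assumed to act on preterm birth only through these, the class 3 NICU RR was 1.09 with none of the three covariates, and 1.00 with diabetes and hypertension even without gestational age. With some additional preterm effect the figures were 1.17 with none, 1.07 with those two and 1.01 with all three. This also stands: removing gestational age alone may not give the total effect.

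Third, the plan does not contradict itself. A reader might infer that it breaks its own birthweight rule, but that rationale is written for cesarean delivery only, and the stated objective is to describe a relationship and compare predictors. Associations conditional on week of birth are a legitimate choice if labelled so. For hypertension and diabetes, adjustment is inferred from one general sentence. Read literally, that sentence would put hypertension in its own model, so it cannot be a complete list. It is still the only rule the document gives for them.

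**Conclusion.** The point holds for NICU admission, for the listed newborn outcomes that meet the events threshold, and, by the general rule, for hypertensive disorders and diabetes. The newborn BMI relative risks will leave out the route through early birth. Those for hypertension and diabetes will be conditioned on a consequence of the outcome. On assumptions not in the documents, the loss is roughly a 5% to 25% indirect NICU excess, and about 0% to 20% of the hypertension excess. No figure was derived for diabetes.

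Three stronger readings are not supported:

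- That every secondary model except preterm birth is certain to keep gestational age. A rare outcome may get a reduced or univariable model.
- That newborn relative risks will fall below 1. With a direct effect of 1.2 the adjusted estimate stays near 1.2. Without a direct effect it falls to about 1, and checks with an unmeasured common cause gave no more than small departures below that (0.97 to 0.999).
- That induction suffers the same fault. Gestation also prompts induction, so the direction is mixed.

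Only secondary outcomes are affected. The correction is worth making because it is cheap, and because a near-null newborn result could otherwise be misread.

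**What to change.** - For each newborn outcome, and for hypertensive disorders and diabetes as outcomes, add a model that supplies the BMI-class relative risks. Use pre-pregnancy BMI whatever the AIC choice, and leave out gestational age and BMI gain.
- For newborn outcomes, also leave out diabetes and hypertension if the result is reported as a total effect.
- For hypertension and diabetes, write out the covariate list and do not include the outcome as its own covariate.
- Do not drop gestational age from any model that contains delivery BMI or BMI gain.
- Keep the planned gestational-age-adjusted newborn models for the BMI-gain term, and label their results as conditional on week of birth.

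The cost is wording in the analysis plan and one extra model per affected secondary outcome. No new data are needed.
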